##### Current activity level

We will use the modified version of the Godin Leisure Time Exercise Questionnaire which has been shown to be a reliable and valid self-report measure of physical activity [45]. The questionnaire contains three questions that assess the average frequency and duration of mild, moderate, and strenuous exercise during free time in a typical week Godin et al. reported the test-retest reliability coefficient of the Godin questionnaire to be 0.64 and the concurrent validity to range from 0.38 to 0.54 over three validity criteria [45].

Accelerometry will be used to monitor 7 days of activity at Week 0, Week 8 (immediately post intervention) & 3 months post intervention. We will use the RT3 accelerometer (Stayhealthy Inc.) which has been shown to be reliable [46] and valid [47]. The RT3 accelerometer measures activity in three dimensions. With the RT3 worn on the hip, the vectors are as follows: vertical (x), antero-posterior (y), and medio-lateral (z) and generates a summary variable-vector magnitude.

##### Cancer-related fatigue

We will use the 13-item Functional Assessment of Chronic Illness Therapy Fatigue Scale (FACT-Fatigue) of the Functional Assessment of Chronic Illness Therapy measurement system which has been developed specifically for the cancer population [42,48]). The reliability of the FACT-fatigue scale has been reported to be 0.84 and it has been shown to have good validity with other measures of fatigue, a significant negative relationship with vigor and with social desirability [49].

##### Satisfaction

Self-administered questionnaire on completion of programme will be administered. Participants will also be asked to highlight what they liked about the programme, what they didn't like, and suggestions for change.

##### Demographics to be recorded

Self-reported socio-demographic variables will include age, gender, ethnicity, employment status, smoking & alcohol habits. Medical information will include co-morbidities and disease variables such as cancer grade, stage and regimen (chemotherapy, radiation therapy, hormonal therapy) will be collected from medical charts.

##### Additional details to be recorded

Protocol deviations, modifications made to any of the exercises will be recoded. Safety is paramount and any adverse events will be reported. We are aiming for a withdrawal and drop-out rate of < 10%. Protocol deviation such as switching or contamination, subjects dropping-out or adhering non-perfectly will also be recorded. The following details on compliance and adherence will also be recorded; compliance (X% of exercise sessions attended and successfully completed), adherence: we are aiming for adherence to exercise intervention (attendance or completion of exercise session) of > 70%.

### Exercise Training Interventions

The class will be supervised by a physiotherapist and a research assistant. There will be a maximum of 10 participants in each class, giving a ratio of at most 1:5 instructor: patient ratio.

The warm-up will consist of performing the mode of exercise prescribed for the work phase at a low intensity to allow the cardiopulmonary system to adapt to the new demand and to allow the temperature of the muscles to increase. Warm-up will be 7-10 minutes duration but slightly longer at the, initial stage of training.

#### Exercise intervention

The class will take 1 hour in total, with an aerobic component of 20-40 minutes increasing on a weekly basis (Table 1). The type of exercise will be continuous, rhythmic exercise using large muscle groups. There will be 3 aerobic stations: including treadmills, cycle ergometer, and rowing machine or stepper or other aerobic exercise such as marching on the spot deemed suitable by the class instructor.

**Table 1 T1:** Progression of the intensity & duration of the exercise class

Intensity	Poor	Fair	Average
**Week 1**	35-55% HRR	40-60% HRR	45-65% HRR
	21 mins aerobic	21 mins aerobic	21 mins aerobic

**Week 2**	35-55% HRR	40-60% HRR	45-65% HRR
	24 mins aerobic	24 mins aerobic	24 mins aerobic

**Week 3**	40-60% HRR	45-65% HRR	50-70% HRR
	24 mins aerobic	24 mins aerobic	24 mins aerobic

**Week 4**	40-60% HRR	45-65% HRR	50-70% HRR
	30 mins aerobic	30 mins aerobic	30 mins aerobic

**Week 5**	45-60% HRR	50-65% HRR	55-70% HRR
	30 mins aerobic	30 mins aerobic	30 mins aerobic

**Week 6**	45-60% HRR	50-65% HRR	55-70% HRR
	36 mins aerobic	36 mins aerobic	36 mins aerobic

**Week 7**	50-60% HRR	55-70% HRR	65-75% HRR
	36 mins aerobic	36 mins aerobic	36 mins aerobic

**Week 8**	50-60% HRR	55-70% HRR	65-75% aerobic
	42 minutes aerobic	42 minutes aerobic	42 minutes aerobic

The class frequency will be twice per week and as well as exercise in the home environment, starting with at least 1 other day (alternating) exercise building up to 3 other days per week. Exercise in the home environment can be carried out in multiple sessions (but no less than 10 minutes each time). A polar watch will be worn during these exercise sessions to monitor intensity.

### Statistical analysis

Randomization will be by a computer-generated random numbers list (GraphPad Software, San Diego, CA) with intention-to-treat as the primary analysis and per protocol as the secondary analysis.

Assuming a difference of 5 mL/kg/min^-1^, with a SD of 6.5, and a 5% significance (two-sided) and 80% power, 28 participants would be required per group. However, the goal would be to accrue 32 subjects to allow for a 15% drop out rate and subgroup analyses. One year will be allowed for accrual of participants. The drop-out rate is calculated to include patients who are unfortunately diagnosed within 3 months of the final assessment as having a relapse of their cancer. As occult return of cancer could have a negative impact on fitness and capacity to exercise, these patients' data will be excluded from the primary outcome measure but included in the process analysis. The same will be done for the data of any participant on anti-Her2 therapy in whom an LVEF assessment during the study or within 3 months of the end of the study has a drop in LVEF to < 50% or by > 20% compared to baseline, as, similarly, occult ongoing myocardial toxicity could have a negative impact on fitness.

We will provide descriptive data and 95% CIs for all possible comparisons. For our primary analysis, we will use the intent-to-treat principle and for the secondary analysis, per-protocol analysis. In sensitivity analyses (intent-to-treat), the impact of missing values will be studied by using a range of imputed change scores for missing values, and by analysing those subjects who provide complete data. Repeated measured of analysis (ANOVA) will be used across more than two time points for continuous data. Mixed-model analysis will be used to model each outcome measure at three (or two) time points and compare the differences across groups over time for non-continuous data. We will use t-tests between 2 groups when data are normally distributed and the Mann-Whitney U test will be used when data are non-normally distributed. The Chi-squared test will be used for categorical data. Tests for interaction will be carried out for the effect of gender and type of cancer.

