**Methods/design:**

The aim is to recruit 64 cancer survivors 2-6 months after completion of chemotherapy, usually adjuvant, with curative intent. Subjects will be recruited through oncology clinics in a single institution and randomised to usual care or an exercise intervention. The exercise intervention consists of two specifically tailored supervised moderate intensity aerobic exercise sessions weekly over 8-weeks. All participants will be assessed at baseline (0 weeks), at the end of the intervention (8 weeks), and at 3-month follow-up. The primary outcome measure is fitness, and secondary patient-related outcome measures include fatigue, quality of life, and morphological outcomes. A further secondary outcome is process evaluation including adherence to and compliance with the exercise program.

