### Inclusion criteria

(i) Diagnosis of solid tumour and completion of adjuvant chemotherapy or radiotherapy with curative intent within the preceding 2-6 months. Patients who have received neoadjuvant chemotherapy or chemoradiotherapy followed by surgery will also be eligible. Patients continuing onto adjuvant hormone therapy and anti-Her2 directed therapy are eligible

(ii) Ability to understand English

(iii) Willing to be randomised

(iv) Medical clearance to exercise

(v) Age 21-69

(vi) Fitness level average, fair or poor according to certain pre-determined cut-off points for age and gender[37]

(vii) Willing and able to attend supervised exercise sessions twice weekly for a period of 8 weeks, with an intention of achieving > 90% attendance

(viii) LVEF > 50% and not < 20% worse than baseline in applicable patients

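### The stated primary comparison names no covariates, although baseline fitness and gender are known before randomisation. This is valid but gives up precision that baseline adjustment would recover.

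*Protocol article*

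**What the plan says.** All of the following is in the protocol article.

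- **Allocation (Statistical analysis).** "Randomization will be by a computer-generated random numbers list". Blocks, strata and minimisation are neither mentioned nor ruled out.
- **What is known before allocation (Patient Recruitment; Inclusion criteria).** The Modified Bruce test is done at screening, and only people at or below the norm for their age and gender are randomised. Criterion (vi) reads "Fitness level average, fair or poor according to certain pre-determined cut-off points for age and gender". Table 1 then sets exercise intensity by the same three categories.
- **Analysis (Statistical analysis).** Repeated-measures ANOVA is named for continuous data at more than two time points, and t-tests or Mann-Whitney tests for two-group comparisons. No covariate is named, and the text does not say whether the two-group tests use raw or change values. Gender enters only here: "Tests for interaction will be carried out for the effect of gender and type of cancer".
- **Sample size (Statistical analysis).** "Assuming a difference of 5 mL/kg/min^-1^, with a SD of 6.5", with "5% significance (two-sided) and 80% power, 28 participants would be required per group". The target is then raised: "the goal would be to accrue 32 subjects to allow for a 15% drop out rate and subgroup analyses". The abstract's total of 64 makes this 32 per group.

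**The concern.** The trial is small, its population is described as heterogeneous, and its outcome is fitness. The article itself treats gender and starting fitness as bearing on that outcome: the cut-offs are gender-specific and training intensity follows the fitness category. Moderate chance imbalance is likely enough at this size. With 32 per arm, a factor carried by half the patients differs between arms by 15 or more percentage points with probability 21%. If the factor is prognostic, an unadjusted comparison carries that imbalance as noise.

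Precision is the stake. The margin is thin: 32 x 0.85 = 27.2, so about 27 per arm remain after the planned drop-out, with t-test power of about 79%. The strongest predictor of the outcome is likely to be the participant's own baseline value, which is collected in any case.

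**Working it through.** **1. The plan's own figure.** Inputs: difference 5, SD 6.5, two-sided 5%, power 80%. The exact two-sample t-test needs 27.5, so 28 per group, with power 80.7%. The figure reproduces.

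**2. Does simple, unadjusted analysis fall short of the plan?** The planned standard error at 28 per arm is 6.5 x sqrt(2/28) = 1.74. In simulations of 56 patients with coin-toss allocation and an unadjusted test, gender and fitness category together explained a share R2 of outcome variance. The documents do not give R2, so a range was assumed, with the total SD held at 6.5.

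| R2 | SE | Type I error | Power |
|---|---|---|---|
| 0 | 1.75 | 4.9% | 80% |
| 0.2 | 1.78 | 5.5% | 80% |
| 0.4 | 1.74 | 5.0% | 81% |

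Nothing falls below the plan, because 6.5 is a total SD that already includes these differences between patients. Unequal arm sizes also matter little. Under a coin toss for 64, a split of 38:26 or worse has probability 17%, yet mean power falls only from 85.7% (32:32) to 85.2%.

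**3. What baseline adjustment gains.** Let r be the correlation between baseline and 8-week fitness within arm (assumed 0.5 to 0.7), with equal SDs at both times. Relative to 1.74:

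- raw 8-week values: factor 1
- change scores: factor sqrt(2(1 - r))
- baseline-adjusted (ANCOVA): factor sqrt(1 - r^2)

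| r | Raw | Change | ANCOVA | Saving vs raw | Saving vs change |
|---|---|---|---|---|---|
| 0.5 | 1.74 | 1.74 x sqrt(1.0) = 1.74 | 1.74 x sqrt(0.75) = 1.50 | 13% | 13% |
| 0.7 | 1.74 | 1.74 x sqrt(0.6) = 1.35 | 1.74 x sqrt(0.51) = 1.24 | 29% | 8% |

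A simulation with coin-toss allocation, 56 evaluable, 30% men and a gender gap of 4 mL/kg/min (the last two assumed) gave these standard errors across the same correlations:

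- raw values: 1.75-1.77
- change scores: 1.34-1.74
- adjusted for baseline fitness: 1.25-1.54
- adjusted and stratified: 1.24-1.49

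The saving from adjustment is therefore 1 - 1.54/1.77 = 13% to 1 - 1.25/1.75 = 29% against raw values. Against change scores it is 1 - 1.25/1.34 = 7% to 1 - 1.54/1.74 = 11%. The algebra and the simulation agree to within about 2 percentage points.

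**4. Stratifying or adjusting?** These are powers from the step 2 simulation. Adjustment here is for gender and fitness category, without continuous baseline fitness.

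| R2 | Neither | Stratify only | Adjust only | Both |
|---|---|---|---|---|
| 0 | 80% | 81% | 78% | 81% |
| 0.2 | 80% | 83% | 86% | 88% |
| 0.4 | 81% | 85% | 95% | 95% |

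Stratifying while keeping the unadjusted test cuts the true standard error (1.78 to 1.54 at R2 = 0.2; 1.74 to 1.35 at R2 = 0.4). The test does not use that gain: its type I error drops to 2.5% and 1.0%, and power rises by only 3 to 4 points. Adjustment delivers most of the benefit without changing the list.

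**The case against.** A reader might infer that a plain list inflates the error of the primary result. With 30% men and gender gaps of 4, 6 or 8 mL/kg/min (all assumed), the variance of a raw-value comparison is 1.10, 1.23 or 1.48 times that under gender-stratified allocation, which looks like losing 9%, 19% or 32% of the sample. The documents do not support that reading, for four reasons.

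- **No damage to the stated plan.** Those ratios measure a gain forgone against a different design. Ordinary standard errors and p-values already allow for chance imbalance, as step 2 shows.
- **The ratios apply to raw post-treatment values only.** The plan names repeated-measures ANOVA and includes week 0 among its assessments. A stable gender gap cancels in change: at an assumed correlation of 0.7, the corresponding ratios on change scores are 1.02, 0.99 and 1.01. The plan also lists plain two-group tests without saying which values they use, so this answers the objection only in part.
- **A plain list is an inference from silence.** A random-numbers list can be blocked or stratified, and a condensed article may leave that to the full protocol.
- **The gender interaction test gives little further support.** Stratifying does not add men. With 19 men among 64 allocated 32:32, imbalance raises the interaction variance by about 3% on average.

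All four points stand. They do not answer the remaining gain from baseline adjustment, which holds against change scores as well as raw values and whether or not the list is restricted.

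**Conclusion.** This is an improvement in efficiency, and no error is shown. The stated allocation and tests are valid, type I error is nominal, and the stated 80% power is met at 28 per group. The analysis as described leaves unused a baseline measurement that every participant must have. At 56 evaluable, using it would lower the standard error by about 13-29% against raw post-treatment values, or about 7-11% against change scores.

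The size rests on the assumed correlation of 0.5 to 0.7, which the documents do not give. Because eligibility removes the fitter part of the range, the true correlation could be lower. At 0.3, the same formulas give a saving of 1 - sqrt(0.91) = 5% against raw values and 1 - sqrt(0.65) = 19% against change scores. The benefit of gender and fitness category depends likewise on how prognostic they are. If they explain nothing, stratifying gains nothing and adjusting for them costs about 2 points of power (80% to 78% in step 4).

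**What to change.** **Main change.** Make the primary comparison of 8-week fitness a baseline-adjusted model: ANCOVA, or a mixed model with baseline as covariate. Pre-specify baseline Modified Bruce fitness and gender as covariates. The cost is two model terms and a sentence of text. No new data are needed, and the sample size can stay as it is.

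**Clarification.** State whether the random-numbers list is blocked or stratified.

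**Optional.** If it is not already restricted, generate the list in permuted blocks of randomly varying size, stratified by gender and fitness category (poor/fair versus average, four strata), and keep those factors in the model. In the step 3 simulation this lowered the standard error only from 1.25-1.54 to 1.24-1.49. The cost is a different list and slightly more predictable allocation at a single site, which varying block sizes limit. Stratifying without adjusting is not worthwhile.

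### The margin from 28 to 32 per group is used up by the stated 15% drop-out, so the target does not also provide for subgroup analyses

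*Protocol article*

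**What the plan says.** The sample-size paragraph under Statistical analysis starts from these inputs: "Assuming a difference of 5 mL/kg/min" (the unit is mL/kg/min), "with a SD of 6.5", and "5% significance (two-sided) and 80% power". It concludes that "28 participants would be required per group". The next sentence raises the figure: "the goal would be to accrue 32 subjects to allow for a 15% drop out rate and subgroup analyses". That sentence does not say whether 32 is per group or in total, but the Abstract settles it: "The aim is to recruit 64 cancer survivors", which is 32 in each of two arms.

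The same section says that the drop-out rate is meant to include participants found to have relapsed within 3 months of the final assessment, whose data leave the primary outcome. It also removes certain participants on anti-Her2 therapy whose LVEF falls, without saying whether they are counted in the 15%. It ends with the commitment that "Tests for interaction will be carried out for the effect of gender and type of cancer". It gives no subgroup proportions, no interaction size and no power for these tests.

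**The concern.** One margin of four per group is said to serve two purposes, drop-out and subgroup analyses. If drop-out at the stated rate takes all four, the second purpose has no participants behind it, and the justification credits the design with a property that it lacks.

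What is at stake is how the interaction tests for gender and type of cancer will be regarded. A sample size described as allowing for subgroup analyses tells the reader that these tests were provided for. The design's own inputs suggest that they were not. This is an error in what the article states, not a detail left to an unseen analysis plan.

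**Working it through.** **Inputs from the article (Statistical analysis; Abstract).** Difference 5 mL/kg/min, SD 6.5, two-sided 5%, power 80%, 28 required per group, 32 per group recruited (64 in total), drop-out 15%.

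**1. Reproduce the 28.** The normal approximation is n = 2 × [6.5 × (1.960 + 0.842) / 5]² = 26.5, so 27 per group. The two-sample t-test (noncentral t) gives 79.2% power at 27 and 80.7% at 28. The smallest n reaching 80% is therefore 28, as stated.

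**2. Test the drop-out allowance.**
- Evaluable at 15% loss: 32 × 0.85 = 27.2, so 27 per group and 54 in total.
- Needed to keep 28 at 15% loss: 28 / (1 − 0.15) = 32.94, so 33 per group and 66 in total.
- Loss that 32 does cover: (32 − 28) / 32 = 12.5%.

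The target is one per group short for drop-out alone. Surplus for subgroups: none.

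**3. Effect on the primary comparison.** At 27 per group, power is 79.2% by the t-test (80.7% by the normal approximation).

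**4. Illustrate the subgroup claim.** The following are assumptions, because the article is silent on them: a two-level factor with the same split in both arms, an interaction equal to the full planned effect (5 mL/kg/min), and a single post-treatment comparison with SD 6.5. With n per arm and a share f in one level,

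SE(interaction) = 6.5 × √[2/(n f) + 2/(n(1 − f))],

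and power comes from the noncentral t with N − 4 degrees of freedom. For n = 27 (N = 54):
- 50:50: SE = 6.5 × √(2/13.5 + 2/13.5) = 3.54
- 80:20: SE = 6.5 × √(2/5.4 + 2/21.6) = 4.42
- 90:10: SE = 6.5 × √(2/2.7 + 2/24.3) = 5.90

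| Split | Power, 54 evaluable | Power, 56 evaluable | Power, all 64 |
|---|---|---|---|
| 50:50 | 28% | 29% | 33% |
| 80:20 | 20% | 20% | 23% |
| 90:10 | 13% | 14% | 15% |

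With an interaction half as large (2.5 mL/kg/min), 54 evaluable and a 50:50 split, power is about 11%. An interaction of 5 at 50:50 would need about 8 × 26.53 = 212 evaluable in total for 80% power (normal approximation).

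**5. Tests within a subgroup are a separate matter.** For a treatment difference of 5 in a half-size subgroup (13.5 to 14 per arm), t-test power is about 48-50%. It is lower in a smaller subgroup and higher in a larger one.

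**The case against.** The strongest reply is that the shortfall is a matter of rounding. It is one participant per group and costs less than one percentage point of power against 80%. By the normal approximation the requirement is 27, and 27/0.85 = 31.8, so 32 would cover 15%. The section on additional details to be recorded aims for drop-out below 10%, and at 10% loss 32 leaves 28.8, which meets 28. The first part stands: the primary comparison is not materially harmed. The rest does not rescue the sentence. The article's own requirement is 28 and its own allowance is 15%. Even on the normal approximation 31.8 rounds up to 32, so again nothing is left for subgroups.

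A second reply is that the interaction figures rest on choices that the article does not make. That stands too. The splits and interaction size are assumed. The formula is for two levels, and type of cancer in a mixed solid-tumour population may have more. Baseline adjustment or the planned repeated-measures analysis could raise power, but no correlation is given from which to say by how much. The figures are therefore an illustration and not a property of the trial. They do not depend on the drop-out rate: with no loss at all, interaction power under the same assumptions is at most 33%.

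A third reply is that low interaction power is common in a trial of 64, and that the article quotes no power for these tests. That is fair. Planning the tests is not the fault; saying that the sample size allows for subgroup analyses is.

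A reader might also infer that a non-significant interaction is going to be taken as proof of a uniform effect, and so as support for the Discussion's hope that the programme would transfer to many cancer settings. The article does not say this. It makes that hope conditional on the programme's success and does not tie it to an interaction test. It also already promises 95% confidence intervals for all possible comparisons.

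**Conclusion.** The statement is wrong as written. At the stated 15% loss, 32 per group leaves 27 against a requirement of 28, so drop-out takes slightly more than the whole margin and subgroup analyses receive nothing. This follows from the article's own figures without further assumption. If the LVEF exclusions fall outside the 15%, the margin is tighter still, but the article does not say.

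Two stronger readings are tempting and not supported. The first is that the primary analysis is underpowered: at about 79% against 80% the difference is negligible. The second is that subgroup tests in general have power of about 13-29%. That range belongs only to two-level interaction tests under the assumptions listed above. Within a half-size subgroup, power is about 48-50%.

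This is a correction to the sample-size justification. It is worth making because a stated design property is untrue, but it does not affect the design or the primary analysis.

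**What to change.** In the sample-size paragraph:

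1. Remove subgroup analyses from the reasons given for 32 per group, and say explicitly that 32 is per group.
2. Restate the allowance in one of two ways: 32 per group covers 12.5% loss (4 of 32), or 32 per group gives about 79% power at 15% loss. If the full 15% is to be covered with 28 evaluable, the target is 33 per group (66 in total).
3. Label the gender and cancer-type interaction tests exploratory, and note that the sample size was not set for them. The confidence intervals already promised can carry their reporting.

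The cost is wording only. Unless the 33-per-group option is chosen, which adds two participants, recruitment does not change. The stated figures become slightly less favourable.

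### The primary analysis is labelled intention-to-treat, but participants with a later relapse or (on anti-Her2 therapy) an LVEF fall are excluded from the primary fitness outcome

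*Protocol article*

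**What the plan says.** Everything at issue is in the Statistical analysis section of the protocol article.

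- The randomisation sentence sets up the analysis "with intention-to-treat as the primary analysis and per protocol as the secondary analysis". A later paragraph repeats it: "For our primary analysis, we will use the intent-to-treat principle and for the secondary analysis, per-protocol analysis".
- Between these two statements come the exclusions. The first concerns patients "diagnosed within 3 months of the final assessment as having a relapse of their cancer"; their "data will be excluded from the primary outcome measure but included in the process analysis". The reason given is: "As occult return of cancer could have a negative impact on fitness and capacity to exercise".
- The second exclusion reads: "The same will be done for the data of any participant on anti-Her2 therapy in whom an LVEF assessment during the study", or up to 3 months after the study ends, "has a drop in LVEF to < 50% or by > 20% compared to baseline". The reason is parallel: undetected continuing myocardial toxicity might lower fitness.
- Relapsed patients are counted inside the 15% drop-out allowance.
- The sensitivity analyses described as intent-to-treat cover imputed change scores for missing values and an analysis of complete data. Neither is said to bring back the excluded participants.

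**The concern.** Intention-to-treat means that everyone randomised is compared in the allocated arm, whatever happens later. Here two groups leave the primary outcome because of something learned after allocation. Three features make this more than a labelling slip.

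1. The exclusions are tied to the outcome. Participants are removed because they are expected to be less fit, and fitness is the primary outcome.
2. They use later information. The last scheduled assessment is the 3-month follow-up (Assessment section), yet an event up to 3 months after it can delete fitness values already measured. The primary analysis set stays open until then.
3. Nothing in the plan restores these participants, because the sensitivity analyses address values that are missing, not values that were measured and set aside.

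At stake is whether the headline fitness difference is protected by randomisation. The trial is described as pragmatic, and a clinician referring a patient cannot know who will later relapse, so a result conditioned on no later relapse answers a different question.

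**Working it through.** **Inputs from the Statistical analysis section.** Planned difference 5 mL/kg/min; SD 6.5; two-sided 5% significance; 80% power; 28 per group; accrual goal 32, read as per group because the Abstract gives a total of 64; drop-out allowance 15%.

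**The plan's own figure.**
- Normal approximation: n = 2 × (1.96 + 0.8416)² × 6.5² / 5² = 26.5, so 27 per arm.
- Two-sample t-test: 27.5, so 28 per arm. This matches the stated 28.
- Allowance: 28 / 0.85 = 32.9, so 33, against a stated 32. The gap of one is immaterial here.

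**Shift caused by the exclusions.** Let an arm of 32 have mean m, and remove k participants whose average is m − d. The mean of those left is

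(32m − k(m − d)) / (32 − k) = m + k × d / (32 − k).

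If the same k and d apply in both arms, both means rise equally and the difference is unchanged. If only one arm loses participants, the difference moves by k × d / (32 − k): upward for exercise if they leave the exercise arm, downward if they leave usual care.

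The document gives neither k nor d. Taking k = 1 or 2 and d = 5 or 10 (about 0.8 and 1.5 SD) as assumptions:

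| k removed from one arm | d (mL/kg/min) | Shift (mL/kg/min) | Share of planned 5 |
|---|---|---|---|
| 1 | 5 | 5/31 = 0.16 | 3% |
| 1 | 10 | 10/31 = 0.32 | 6% |
| 2 | 5 | 10/30 = 0.33 | 7% |
| 2 | 10 | 20/30 = 0.67 | 13% |

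**Scale against sampling error.** At 32 per arm the standard error of the difference is 6.5 × √(2/32) = 1.63, so the largest shift is 0.67 / 1.63 = 0.4 standard errors.

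**Effect on the false-positive rate.** At 28 per arm the standard error is 6.5 × √(2/28) = 1.74. With no true effect and a nominal 5% two-sided test (normal approximation), a bias of 0.25 gives a rejection rate of 5.2%, 0.5 gives 6.0% and 0.75 gives 7.2%. The shifts in the table all lie below 0.75.

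**Cost in power of keeping everyone.** At the planned difference and SD, t-test power is 80.7% with 28 per arm and 85.7% with 32.

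**The case against.** The best defence is that the rules are pre-specified, openly stated, narrow and the same in both arms. They also echo eligibility: the Exclusion criteria bar active cancer and use the same LVEF thresholds, so the authors may see these participants as people who were never truly in the target population. That is a coherent motive, and the choice of target population is partly a design decision. It does not rescue the label. The triggers can occur up to 3 months after the last visit, nothing shows that the condition was present at randomisation, and the text does not call the analysis modified intention-to-treat.

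The defence does succeed against several stronger readings that a reader might infer:

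- *The randomised comparison is lost altogether.* Not supported. With balanced exclusions and deficits the bias is zero, and with few exclusions it is small.
- *Class contact makes detection unequal between arms.* Speculative. Supervised classes last 8 weeks, while the relapse window runs past the 3-month follow-up. LVEF is found by a cardiac measurement, and nothing says that usual-care participants have less oncology follow-up.
- *Harm from exercise would be hidden.* Not supported. The section on additional details to be recorded says that adverse events will be reported, and the process analysis keeps these participants.
- *Restricting the LVEF rule to anti-Her2 participants is arbitrary.* Weakly supported. The stated reason is continuing toxicity, and no on-study LVEF measurement is scheduled for others.
- *The plan itself implies 1 or 2 exclusions per arm, from 15% less the drop-out aim of under 10%.* This subtracts an aim from a sample-size allowance. Relapses are said to be inside the 15%; LVEF exclusions are not clearly so, and the 32 also serves subgroup analyses. The count has to remain an assumption.

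**Conclusion.** The point holds as a contradiction within the Statistical analysis section: the primary analysis is called intention-to-treat, and the exclusions fixed beside that label mean that it is not. They follow randomisation and relate to the outcome, so the protection of randomisation is given up for the primary outcome. The contradiction rests on the text alone and on no assumption.

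The size does rest on assumptions. With 1 or 2 of 32 removed from one arm only, each 5 to 10 mL/kg/min below the full arm mean, the shift is about 0.16 to 0.67 mL/kg/min, or 3 to 13% of the planned difference. One-sided removal is the unfavourable case; balanced removal gives none. The direction cannot be known in advance. A bias of this size would probably not overturn a true difference of 5, but it is avoidable and sits in the primary result.

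**What to change.** 1. Delete both exclusions from the primary analysis. Analyse all randomised participants in the allocated arm with every fitness value measured, whatever the later relapse or LVEF finding.
2. Handle participants who could not be tested through the missing-data sensitivity analyses already in the plan.
3. Keep the analysis without relapse and LVEF cases as a pre-specified sensitivity (or per-protocol) analysis, labelled as such.
4. Report relapses and LVEF falls by arm.
5. Reword the sentence on the 15% allowance so that relapsed patients with measured fitness are not counted as drop-outs.

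The cost is wording in one section. The downside is a slightly larger outcome variance from a few unwell participants, and possibly a slightly smaller mean difference. No extra patients are needed: power at the planned difference and SD is about 81% at 28 and 86% at 32 per arm.
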